# Study protocol of a randomized controlled trial of motivational interviewing-based intervention to improve adherence to continuous positive airway pressure in patients with obstructive sleep apnea syndrome: The MotivAir study

**DOI:** 10.3389/fpsyg.2022.947296

**Published:** 2022-08-25

**Keywords:** sleep disorders, obstructive sleep apnea syndrome, continuous positive airway pressure, motivational interventions, adherence to CPAP, randomized controlled trial, randomized control trials (RCTs)

## Abstract

**Objective:**

This study aims to evaluate the effectiveness of the MotivAir program—a phone-based intervention based on Motivational Interviewing (MI) principles and techniques—in enhancing adherence to Continuous Positive Airway Pressure (CPAP) therapy among patients with Obstructive Sleep Apnea Syndrome (OSAS).

**Methods:**

A multicenter randomized controlled trial (RCT) design with random allocation at the level of the individual will be conducted to compare the impact of the experimental program (usual care *plus* MI) with a control group receiving usual care only in improving selected clinical and psychological parameters in the patients. A minimum sample of 80 participants (40 patients per group) will be recruited in each center according to the inclusion criteria. After the initial screening, participants will be randomly assigned to either the experimental group or the control condition. The program will last 180 days and will be delivered by a trained nurse. The impact of the MotivAir program on selected primary (adherence to CPAP in terms of average hours of usage per night and the Apnea-Hypopnea Index, AHI) and secondary (motivation, perceived competence, quality of life, sleepiness) outcomes will be measured at baseline, and after 1-, 3-, and 6-month from CPAP initiation.

**Discussion:**

Participants are expected to show an increased level of adherence to CPAP and to acquire the skills and self-confidence necessary to deal with the psychological consequences of their chronic condition.

## Introduction

Obstructive sleep apnea syndrome (OSAS) is a chronic illness characterized by a complete or partial obstruction of the upper airway. It has been demonstrated to be a risk factor for several diseases—including hypertension, impairment of cognitive functions, ischemic heart disease, and stroke (Garvey et al., 2015)—and to be correlated with other non-medical consequences—such as work-related injury, and motor vehicle crash (Garbarino et al., 2015, 2016)—that increase OSAS’s clinical and economic burden. Also, persons with OSAS often exhibit a poor health-related quality of life (HRQoL) (Lo Bue et al., 2020), which has a demonstrated negative impact on physical health outcomes (e.g., negative health perceptions, increased bodily pain, and poor physical functioning) and psychosocial functioning (e.g., mood disturbance, poor academic performance, and reduced social life) of individuals with OSAS (Timkova et al., 2020). In Italy, despite the impact of OSAS is highly underestimated due to substantial diagnosis gaps—it affects 27% of the adult population, of which 65% are males (Armeni et al., 2019).

Continuous positive airway pressure (CPAP) is the first-line treatment for moderate/severe OSAS. It increases the individuals’ clinical parameters and HRQoL by eliminating daytime sleepiness, and also decreases morbidity and mortality rates related to cardiovascular diseases (Luyster, 2017; Morsy et al., 2019; Lo Bue et al., 2020). Still, the effectiveness of the device is often limited by suboptimal adherence (Gay et al., 2006; Giles et al., 2006). Indeed, it has been suggested that improvements are more consistent with over 5.5 h of usage per night (Batool-Anwar et al., 2016; Bakker et al., 2019), but the literature reports that between 29 and 83% of patients enrolled in research studies use CPAP < 4 h per night (Bakker et al., 2016; Weaver, 2019) or refuse treatment (Baratta et al., 2018; Rezaie et al., 2021).

Adherence to CPAP treatment depends on several factors, including individual characteristics, features associated with the device (Crawford et al., 2014; Batool-Anwar et al., 2016) and its side effects, as well as psychological and social determinants (Crawford et al., 2014; Sanna and Lacedonia, 2018).

Understanding barriers and facilitators to CPAP adherence is vital for the development of effective interventions. Over the years, it has become evident that suboptimal adherence is largely predicted by psychological measures of behavior change—including motivation and perceived self-efficacy (Philip et al., 2018; Wong et al., 2020; D’Rozario et al., 2021). For example, in a multiethnic sample of 248 patients, self-efficacy (which describes the extent to which a patient believes that he or she is capable of attaining positive outcomes from treatment) was significantly associated with adherence to CPAP after adjusting for several other potential determinants (Wallace et al., 2013).

Motivational Interviewing (MI) is often used in healthcare settings to increase motivation to change and self-efficacy in patients with chronic illnesses (Pietrabissa et al., 2012, 2013, 2015; Pietrabissa, 2018; Nedjat-Haiem et al., 2019; Scott et al., 2019), and has a demonstrated positive impact in increasing adherence to CPAP among patients with OSAS (Miller and Rollnick, 2002, 2013; Rapelli et al., 2021). Consistent with several models of behavior change, including the transtheoretical model of change (TMC, Prochaska and DiClemente, 1983), this approach is mainly aimed at addressing the individuals’ inner ambivalence to change. Expressing empathy, developing discrepancy, rolling with resistance, and supporting self-efficacy are the principles encompassed by MI on which intervention strategies with existing empirical support (Olsen et al., 2012) are based to help patients to develop specific goals and increase their readiness to change.

A few studies have considered adherence to CPAP as compliance maintained over time correlated with disease awareness and change to a healthier lifestyle (e.g., Weaver and Sawyer, 2010) but to our knowledge, even fewer are studies that address these aspects in correlation with technological advances such as telemonitoring and telephone assistance (e.g., Hu et al., 2021). However, the recent study conducted by Hwang et al. (2018) shows that telemonitoring with automated feedback messages improved adherence to CPAP at 90 days in OSAS patients. Furthermore, beyond the single clinical and sociodemographic factors, the studies of Aloia et al. (2007) and Budhiraja et al. (2007) indicate that long-term adherence is determined by the results conquered in the first 2 weeks of treatment. In fact, telemedicine interventions and action plans provided at home are increasingly supporting patients in health communication, self-monitoring, and self-treatment. These interventions have made information easily accessible, helping patients to early detect symptoms, with more timely treatment, reduction in hospitalizations, and improved health-related quality of life (Hu et al., 2021). Furthermore, telemedicine-based interventions may be able to facilitate assisting patients with physical limitations and those who need a frequent evaluation of their health status. They also have the potential to foster greater patient engagement and less costly interventions (Hu et al., 2021). Although more research into the effectiveness of these telemedicine interventions is still needed because research in patients with OSAS is underdeveloped.

More investigations should focus on the use of the different formats of delivering motivational interventions including the use of new technologies, in fact to our knowledge results regarding the effects of remote-MI interventions for naïve patients using CPAP are still scant and inconsistent. Furthermore, only one RCT (Sparrow et al., 2010) tested the effect of a MI-based intervention using telemedicine in the long-term after 12 months from CPAP initiation, and collected interesting results. In fact, research that can effectively be provided digitally to patients with OSAS using CPAP could represent advantages and reduced costs (Appel et al., 2011; Bus et al., 2018).

Concerning the educational and formative aspects, Olsen et al. (2012) applied an educational program to naive patients that integrated the MI—which was recognized as best practice by the Agenzia di Tutela della Salute of Lombardy in Italy for the promotion of a healthy lifestyle—based on the work of Rollnick and Miller (1995) with the modifications indicated by Aloia et al. (2004) for OSAS patients.

For these reasons, we develop the MotivAir project—a phone-based motivational intervention that integrates telemedicine and telephone assistance based on MI principles and techniques to support adherence to CPAP in naïve patients with OSAS. This is the first study in Italy that will use MI-based intervention for OSAS patients by integrating telemedicine and telephone assistance and in-person sessions. Furthermore, it will be based on personalized care plans in response to the patient’s profile (e.g., patient age, socio-demographic variables, and distance to hospital) and this approach could identify who needs intensive care and further increase CPAP adherence. A personalized-based intervention represents a golden standard for the cost-effective impact, but only one study has been achieved with personalization of care for patients with OSAS using CPAP.

Rudilla et al. (2021b) already showed increased compliance with the device, as well as increased self-efficacy, and quality of life in terms of daily activities, and social relationships in CPAP-naive patients with severe OSAS after receiving a personalized motivational intervention plan. The purpose of this randomized controlled trial (RCT) will be to determine whether MI-based strategies delivered by a nurse, and added to a standard pulmonary rehabilitation program, will be superior to usual care in improving adherence to CPAP. Specifically, we hypothesize that adding MI feedback to standard care will result in improved adherence to CPAP in terms of average hours of usage per night and increased Apnea-Hypopnea Index (AHI) after 90 days from CPAP initiation. We also hypothesize that results will be maintained or increase at 6 months of follow-up and that patients will also show increased levels of motivation, perceived competence, and sleepiness.

## Methods/design

The effectiveness of the MotivAir program will be assessed in a multi-center randomized controlled study with two arms: an experimental arm with TAU plus personalized MI carried out by a trained nurse (MotivAir group), and a TAU control.

The study was approved by the Ethical Committee of the Istituto Auxologico Italiano, Italy (ID: 2021_03_23_02). All procedures performed in the study will be run following the ethical standards of the institutional and/or national research committee and with the Helsinki Declaration and its later amendments or comparable ethical standards.

## Study population

All patients diagnosed with OSAS and CPAP referring to the IRCSS Istituto Auxologico Italiano, San Giuseppe hospital, and San Luca Hospital will be screened for admission into the study during their first week of a pulmonary rehabilitation program. Patients will be eligible if meeting the following inclusion criteria: (1) being over 18 years old; (2) have a diagnosis of OSAS confirmed by polysomnography; (3) being recommended for treatment with CPAP; (4) being naïve to this type of intervention; (5) being fluent in the Italian Language; and (6) having signed the written informed consent to participate in the study. Exclusion criteria will be: (1) use of oxygen therapy > 2 l/min; (2) history of severe cognitive disorders; (3) history of COPD: FEV1/FVC (Tiffeneau Index) ≤ 60% with FEV1 ≤ 50%; (4) dyspnea on exertion (Borg > 6); (5) diagnosis of Long COVID or COVID-19 infection < 4 months; (6) chronic heart failure (NYHA: Grade III and IV); (7) unstable ischemic heart disease; 8) presence of visual, or hearing impairments that will prevent the patients from following the intervention and filling in the questionnaires.

Before enrolling in the study, all patients will be informed in detail about the study criteria and procedure and will be asked to sign the consent form to participate.

## Randomization procedure

Randomization will be stratified within each center through permuted randomized blocks. Randomization will take place after the baseline measurements (Figure 1).

**FIGURE 1 F1:**
[figure not shown]
Flow chart of the MotivAIR study.

## Sample size calculation

A sample of 80 patients (40 in each group) will allow detection as a significant effect size of 0.67 (based on the average daily difference in apnea hours between groups) measured at the 6-month follow-up, a first type error of 0.05, a power of 80% and a drop-out of 10%. Data related to the effect size were retrieved from the PIMA study (Rudilla et al., 2021b), while the mean daily difference in apnea hours and the standard deviation were provided by the researchers. The sample size was assessed using PASS 14 software (Power Analysis and Sample Size Software (2015). NCSS, LLC. Kaysville, Utah, United States, ncss.com/software/pass).

### Measures

*Demographic information* about age, gender, education, and civil status will be self-reported at baseline.

*Clinical variables* will be recorded during the initial visit with the physician and retrieved by the patients’ medical records by a clinical psychologist working in the clinic, independent from the study. They will include the (1) *Epworth Sleepiness Scale* (ESS; Johns, 1991; Vignatelli et al., 2003) as a measure of daytime sleepiness. Respondents will be asked to rate, on a 4-point scale (0–3), their usual chances of dozing off or falling asleep while engaged in eight different activities. The ESS score can range from 0 to 24. The higher the ESS score, the higher that person’s average daytime sleepiness; and the (2) *Apnoea-Hypopnea Index (AHI)*, which determines the presence and severity of OSAS.

### Primary outcome

The primary outcomes of this study will be the participants’ *adherence to CPAP therapy* (mean hours/night) and the AHI score after 180 days from the treatment beginning. CPAP usage (hours/night) will be automatedly recorded by the device, while AHI will be measured by polysomnography during follow-up visits at the hospital.

Data will be also analyzed after 30 and 90 days of treatment as a secondary outcome.

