In addition, subjects in the MotivAir group will follow a telephone-based intervention—lasting ~45 min—based on MI principles and techniques delivered by a nurse. For the specific purpose of the study, the nurse will preliminarily receive 8 h of MI training provided by two psychologists experts in the MI approach (authors GR and GP). During the training, the nurse will learn about the collaborative, evocative, and client-centered spirit of MI, and the characteristics that define each stage of change and will be instructed to apply the basic communication and listening skills of this approach (open-ended questions, affirmations, reflective listening, summarizing). Then she will learn to reinforce and elicit change talk, while also responding in ways that reduce counter-change talk and to roll with the patients’ inner resistance to change by affirming the patients’ autonomy and reflecting their resistant speech with empathy. Next, the issues of how and when to introduce the development of a change plan, and enhance the individuals’ commitment to change will be addressed.

The treatment plan will be implemented based on each patient’s level of adherence. To low adherence (score below 16 on the ESS and CEPCA questionnaires) a more intensive telephone-based assistance (days 1, 8, 16, 30, 90, 120, 180 from the end of the rehabilitation period) will follow. In the case of high adherence (score greater than or equal to 16 on the ESS and CEPCA questionnaires), phone encounters will be set on days 1, 8, 30, 90, and 180 after treatment termination.

At 1-, 3- and 6-month follow-up, adherence to the device will be assessed by automatedly recorded CPAP usage (hours/night) and AHI. Changes in the selected psychological variable will be also examined.

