## Statistical analysis

Descriptive statistics (means ± SD, or median and interquartile ranges, as appropriate) will be used to describe the study sample with regard to baseline characteristics. Before selecting the most appropriate statistical tests, assumptions for parametric analyses will be checked. Continuous variables will be reported as mean and standard deviation (or median and interquartile range when needed). Categorical variables will be reported as absolute and relative frequency. The mean daily apnea hour will be compared between groups by repeated-measures analysis of variance. To account for the correlation of within-patient measurements, a linear mixed model with a covariance variance matrix chosen based on the lowest Akaike Information Criterium (AIC) index value will be used. The model will also possibly include some characteristics of patients that are found to influence the level of expected adherence identified with preliminary multinomial logistic regressions. All tests will be two-tailed and the *p*-value will be significant if less than 0.05. Analyses will be conducted with SPSS statistical software.

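### Two primary outcomes are named, every test is judged at 0.05 and the sample size covers one variable; with no success rule, neither the 5% error nor the 80% power is guaranteed for the primary claim

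*Protocol article*

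**What the plan says.** - **Two primaries.** The Primary outcome section gives CPAP use and AHI equal standing: "mean hours/night) and the AHI score after 180 days from the treatment beginning". The Abstract (Methods) also lists both as primary: "adherence to CPAP in terms of average hours of usage per night and the Apnea-Hypopnea Index, AHI".
- **One threshold for everything.** Statistical analysis states: "All tests will be two-tailed and the *p*-value will be significant if less than 0.05". It gives no order of testing and no division of alpha.
- **One sized variable.** Sample size calculation says that 80 patients, 40 per group, "will allow detection as a significant effect size of 0.67 (based on the average daily difference in apnea hours between groups"), with "a first type error of 0.05, a power of 80% and a drop-out of 10" percent. It gives no effect size for AHI.
- **Naming.** Sample size calculation and Statistical analysis both refer to apnea hours, which is the name of neither primary outcome. Statistical analysis names no between-group comparison for AHI.
- **AHI as adherence.** Procedure says that at follow-up "adherence to the device will be assessed by automatedly recorded CPAP usage (hours/night) and AHI". Under Measures, AHI is instead an index of whether OSAS is present and how severe it is.
- **Total size.** Sample size calculation gives 80 patients. The Abstract gives a minimum of 80 in each center.

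**The concern.** With two primary outcomes, a trial needs a rule for what counts as success. The 5% error and the 80% power are properties of that rule, not of each test taken alone. Here the threshold and the power statement both fit a trial with one primary outcome, while the outcome section names two.

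The choice between the possible rules could therefore be made after the results are known. If a significant result on either outcome may carry the claim, there are two chances of a false positive at 5% each. If both are needed, a trial sized for one can miss a real effect more often than its power statement says. If usage improves and AHI does not, or the reverse, the article gives no agreed way to report the result.

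**Working it through.** **Inputs from the documents.** Effect size 0.67, alpha 0.05, power 80%, drop-out 10%, 40 per group (Sample size calculation); two-sided tests at 0.05 (Statistical analysis); two primary outcomes (Abstract, Primary outcome).

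**Assumptions, not in the documents.** The correlation between the two test statistics is varied from 0 to 0.9. The standardised AHI effect is varied from 0.3 to 0.67. Where the Abstract's wording is used, two centers are assumed.

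**1. The plan's own figure.** A two-sample t-test with d = 0.67 and two-sided alpha 0.05 needs 35.96 evaluable patients per arm for 80% power, so 36. Allowing for drop-out, 36/(1 − 0.10) = 40 per arm, 80 in total. This matches the plan exactly. Power at 36 per arm is 80.05%, so nothing is left over for a second primary outcome.

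**2. Rule A: either outcome suffices, each at 0.05.** For independent outcomes the familywise error is 1 − (1 − 0.05)² = 0.0975. Simulation gives the correlated cases.

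| Correlation | Familywise error |
|---|---|
| 0 | 9.75% |
| 0.5 | 9.1% |
| 0.8 | 7.8% |
| 0.9 | 7.1% |

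These values do not depend on sample size. Power does not fall under this rule. If AHI also had d = 0.67, the chance of at least one significant result would be 1 − (1 − 0.8005)² = 96% for independent outcomes, and about 85% to 86% at correlation 0.9.

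**3. Rule B: both must succeed, each at 0.05.** The error is at most 5%. With 36 evaluable per arm and d = 0.67 on both outcomes, joint power is 0.8005² = 0.641 for independent outcomes. Simulated t-tests give about 69% at correlation 0.5 and 75% at 0.9. A normal approximation runs one to two points higher (66%, 70%, 76%).

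Power for AHI alone depends on an effect that the article does not give:

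| Assumed AHI effect | AHI power, 36 per arm | Joint power if independent |
|---|---|---|
| 0.67 | 80% | 0.8005 × 0.8005 = 64% |
| 0.5 | 55% | 0.8005 × 0.553 = 44% |
| 0.3 | 24% | 0.8005 × 0.241 = 19% |

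**4. Rule C: alpha split, 0.025 each.** At 36 per arm, power for d = 0.67 falls to 70.9% per outcome.

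**5. Sensitivity to total size.** If 80 are recruited in each of two centers, evaluable patients per arm are 2 × 36 = 72. At d = 0.67, power is 97.9% per outcome at 0.05 and 95.9% at 0.025. Joint power for independent outcomes is 0.979² = 96%. With an AHI effect of 0.3, AHI power is still only 43%. The familywise error under Rule A is unchanged.

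**The case against.** **Error and power do not fail together.** A reader might infer that the trial has lost both its 5% error and its 80% power. The documents do not support that. The error is inflated only if either outcome suffices, and the chance of a win then rises. Power is lost only if both are required, and the error then holds. No single rule breaks both. The outcomes are also joined by *and* in the Introduction's hypothesis and in Primary outcome, which fits a both-must-succeed reading at least as well. This stands. It limits the claim to neither property being guaranteed, but *and* in a list of outcomes is not a stated success rule.

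**The power loss is conditional.** It rests on 80 patients in total and on an AHI effect that has to be assumed. Under the Abstract's per-center wording, with two centers, most of the loss goes at d = 0.67. This also stands. It is a reason to reconcile the two statements, and it does nothing for the error under an either-outcome rule.

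**A SAP may hold a multiplicity rule.** It may, and its absence from an article would not be a finding. The point rests on what the article does state: two primaries, a flat threshold for all tests, and a power statement for one variable.

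**AHI as a clinical co-primary is a coherent choice.** The Abstract says that the trial targets clinical as well as psychological parameters. That is fair, but the choice then needs a success rule and an AHI effect.

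**Two stronger readings of AHI are tempting.** One is that the article contradicts itself on the source of AHI. It does not: Primary outcome says "AHI will be measured by polysomnography during follow-up visits at the hospital", and the Procedure sentence can be read as two separate items, recorded usage and AHI. The other is that AHI is uninterpretable because the article does not say whether CPAP is on or off during the recording. That rests on knowledge from outside the documents and on operational detail that an article may leave to the full protocol.

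**Conclusion.** The point holds in a limited form. The article fixes two primary outcomes and a 0.05 threshold for each test, sizes the trial on one variable, and states no success rule. The primary claim therefore has no assured error rate or power.

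- **Either outcome suffices:** the familywise error is 7.8% to 9.75% for correlations from 0.8 down to 0, whatever the sample size.
- **Both required:** the error is at most 5%. Joint power is about 64% to 75%, given 36 evaluable per arm and an assumed d = 0.67 for AHI, and lower for a smaller AHI effect.

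The power figures apply only if 80 is the trial total. Taking apnea hours to mean CPAP hours is an inference, though a likely one. The Procedure wording that lists AHI among the ways of assessing adherence is a smaller fault, because it conflicts with the article's own description of AHI as a measure of disease presence and severity. The main fault should be settled before the data are analysed, since the trial's headline conclusion depends on it.

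**What to change.** 1. Name mean CPAP hours per night at 180 days as the single primary outcome in the Abstract and in Primary outcome.
2. Replace apnea hours in Sample size calculation and Statistical analysis with that outcome, after confirming that the 0.67 refers to it.
3. Make AHI at 180 days the first secondary outcome, tested at 0.05 only if the primary is significant. This fixed order holds the error at 5% over the two tests and keeps the stated 80% power for the primary.
4. Reword Procedure so that AHI is not listed as a measure of adherence.
5. State once whether 80 is the trial total or the number per center.

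The cost is amendment wording. AHI is still collected and loses only its co-primary label.

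If the sponsor prefers to keep both primaries, the success rule, an AHI effect assumption and a matching sample size must be stated. At d = 0.67, 80% power for each outcome at 0.025 needs 44 evaluable per arm: 44/0.9 = 48.9, so 49 per arm and 98 in total. For 80% joint power with independent outcomes and d = 0.67 on both, each test needs power √0.8 = 89.4%. That takes 47 evaluable per arm: 47/0.9 = 52.2, so 53 per arm and 106 in total.

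### Two primary outcomes share an unadjusted 0.05 threshold with no rule for combining them; if either one counts as success, the false-positive rate can reach 9.75%

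*Protocol article*

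**What the plan says.** The Primary outcome section lists CPAP adherence and AHI together as primary outcomes at one time point: "mean hours/night) and the AHI score after 180 days from the treatment beginning". The abstract's Methods paragraph lists the same pair: "adherence to CPAP in terms of average hours of usage per night and the Apnea-Hypopnea Index, AHI".

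The Statistical analysis section sets one criterion for everything. It begins "All tests will be two-tailed and the" and goes on to say that the p-"value will be significant if less than 0.05". The only variable it names for the between-group model is a mean daily *apnea hour*, so AHI is reached only through the blanket sentence on all tests.

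The Sample size calculation section rests on a single variable, an "effect size of 0.67 (based on the average daily difference in apnea hours between groups"), with "a first type error of 0.05, a power of 80% and a drop-out of 10"%. It arrives at "A sample of 80 patients (40 in each group"). It gives no effect size, standard deviation or power for AHI. The abstract states the target differently: "A minimum sample of 80 participants (40 patients per group) will be recruited in each center".

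No section says whether trial success needs one primary outcome or both.

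**The concern.** With two primary outcomes, the meaning of a positive trial depends on a combining rule. Without one, the choice can be made after the results are known. A significant AHI with a null result for CPAP use, or the reverse, could be reported as a positive primary result of an adherence trial. Each claim would satisfy the 0.05 criterion as written, yet the chance of a false claim on at least one outcome would exceed 5%.

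If success instead needs both outcomes, the error rate is safe and the cost falls on power. A sample sized for one variable at 80% does not give 80% for a joint requirement.

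**Working it through.** **Inputs.** From the Sample size calculation: effect size d = 0.67, alpha 0.05, power 80%, drop-out 10%, 40 per group. From the Statistical analysis section: two-sided tests, threshold 0.05. From the Primary outcome section: two outcomes at 180 days. The document gives neither an AHI effect nor the correlation between the two test statistics, so both are varied below as assumptions.

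**1. Reproduce the stated sample size.** A two-sample t-test with d = 0.67, two-sided alpha 0.05 and 80% power needs 35.96, so 36 per arm. Inflating for drop-out, 36 / (1 − 0.10) = 40 per arm, or 80 in total. The stated figure reproduces exactly, and power at 36 per arm is 80.05%. The calculation is correct for one variable at full alpha and contains no allowance for a second primary outcome.

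**2. Error rate if either outcome is enough.** With both null hypotheses true and independent tests, 1 − (1 − 0.05)² = 1 − 0.9025 = 0.0975. For correlated tests, a bivariate normal calculation with critical value 1.96 gives:

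| Correlation | Chance of at least one false positive |
|---|---|
| 0 | 9.75% |
| 0.5 | 9.1% |
| 0.7 | 8.3% |
| 0.9 | 7.0% |

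**3. Error rate if both are required.** A false claim then needs a false rejection on at least one true null together with a rejection on the other outcome, so its probability cannot exceed 5%.

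**4. Power if both are required, 36 analysed per arm.** Suppose AHI also has d = 0.67 (assumption). With independent tests, joint power is 0.8005 × 0.8005 = 0.641. Holding each test's power at 80.05% and joining them by a bivariate normal gives 0.69 at correlation 0.5 and 0.75 at 0.9. With smaller assumed AHI effects and independent tests:

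- AHI d = 0.5: AHI power is 55.3%; joint power is 0.8005 × 0.5526 = 0.442.
- AHI d = 0.4: AHI power is 38.8%; joint power is 0.8005 × 0.3875 = 0.310.

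**5. Sensitivity to the per-center reading.** If the abstract's 80 per center is the target and there are two centers (assumption), the total is 160, and 80 × 0.9 = 72 per arm are analysed. Power at d = 0.67 is then 97.9% at alpha 0.05 and 95.9% at 0.025. Joint power for two independent outcomes, both with d = 0.67, is 0.979 × 0.979 = 0.958. Step 2 does not involve the sample size, so the error rates there do not change.

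**6. Compare remedies at 36 per arm.** Splitting alpha to 0.025 each lowers power for d = 0.67 from 80.05% to 70.9%. Restoring 80% would need 44 analysed per arm, or 44 / 0.9 = 48.9, so 49 per arm and 98 in total. A fixed sequence tests the first outcome at the full 0.05, so its power stays at 80.05%. The second outcome is reached only after the first rejects, which keeps the overall error at or below 5%.

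**The case against.** The strongest reply is that nothing in the article is wrong as stated. A 0.05 threshold for each test is fully compatible with a both-required rule or a fixed sequence, and either would hold alpha. The hypothesis in the Introduction joins the two outcomes with *and*, and nowhere does the text say that one is enough. A condensed article may also leave a combining rule to the analysis plan.

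Part of this stands. The inflation is conditional, and a reader who infers that the type I error is certainly not held goes further than the document does. However, the Introduction's hypothesis concerns 90 days while the primary time point is 180, and it is an expectation, not a decision rule. The article does more than stay silent: it fixes two primary outcomes and an unadjusted threshold for all tests. Followed as written, that lets either be claimed.

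Two other stronger readings are tempting. One is that the sample size section promises a trial-wide 5% error and 80% power and fails to deliver them. It does not promise this: both figures are inputs for one variable, and for that variable they are delivered. The other is that the trial is underpowered. That depends on a both-required rule, on an assumed AHI effect and on 80 patients in total. On the per-center reading with two centers, joint power could be about 96% when both effects are 0.67.

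**Conclusion.** The point holds in conditional form. Two primary outcomes with one unadjusted 0.05 threshold leave the trial's success criterion open, and each way of closing it has a cost that the protocol does not acknowledge.

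- If either outcome suffices, the false-positive rate is 9.75% with independent tests, falling to 7.0% at correlation 0.9. This assumes both nulls are true.
- If both are required, alpha is held. At 36 analysed per arm, joint power is about 64% to 75% across correlations 0 to 0.9 with an AHI effect of 0.67, and about 31% to 44% with independent tests and AHI effects of 0.4 to 0.5. Every AHI effect here is assumed.

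On any reading, the stated 80% covers at most one variable. That variable is called *apnea hours*, which is not clearly either primary outcome. The power figures would improve if 80 per center is the true target; the error-rate figures would not. This should be fixed before outcome data are compared between groups, but it does not invalidate the design or the sample size arithmetic.

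**What to change.** In the abstract's Methods paragraph, the Primary outcome section and the Statistical analysis section, specify a fixed sequence:

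1. CPAP hours/night at 180 days is tested first at two-sided 0.05, and this test decides trial success.
2. AHI at 180 days is tested at two-sided 0.05 only if the first test is significant. Otherwise it is reported descriptively.

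In the Sample size calculation section, name the variable to which the 80% power applies (CPAP hours/night, if that is what *apnea hours* means) and state that it does not cover AHI. Reconcile the total of 80 in that section with the abstract's 80 per center. Align the Introduction's joint 90-day hypothesis with the chosen order and time point.

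The cost is wording only: no extra patients and no loss of power for CPAP use. The downside is that AHI cannot be claimed on its own if CPAP use is null. Requiring both outcomes would also hold alpha, but the sample size would then need an AHI effect assumption and a joint power calculation.
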